### {#13 Participant timeline}

Hospitalized participants are followed through their hospitalization (up to 30 days from the initial ED visit) to identify outcomes. The guardians of participants discharged from the ED will be contacted (by telephone or text) at least 7 days from the initial ED visit to assess their status. We will make up to four attempts by telephone or text to contact the guardians over 3 months after the index ED visit, starting on day 7.

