**Methods:**

This is a multicenter, randomized controlled clinical trial to assess the impact of the FAST examination on the initial evaluation of children with blunt abdominal trauma. Enrolled participants will be randomized 1:1 to the FAST examination plus routine care or routine care alone during their initial emergency department (ED) evaluation. The study will enroll 3194 (initial sample size) to 4346 (second sample size) children at six diverse sites. The primary outcomes are as follows: (1) The proportion of abdominal CT in the initial 24 h of care and (2) the proportion of missed or delayed diagnoses of IAIs. Secondary outcomes include (1) ED length of stay, (2) hospitalization proportion and length of hospital stay, (3) physician suspicion of IAI, (4) the proportion of abdominal CT use in the subgroup of children 0 to 3 years old, and (5) laparotomy proportion. Hospitalized participants will be followed through their stay, and guardians of those discharged from the ED will be contacted after 1 week to assess their status.

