### {#12 Outcomes}

Primary outcomes will be measured and documented in both study arms. These outcome measures are the same as those used in the single-center randomized controlled trial. The primary outcomes are the abdominal CT proportion and the proportion of missed/delayed diagnosis of IAIs. The abdominal CT proportion will be calculated as the number of participants receiving abdominal CT scans in the initial 24 h divided by the number of participants in each arm (i.e., proportion of participants undergoing CT during their initial ED evaluation). Abdominal CT scans will be obtained at the discretion of the treating physicians in the ED. The other primary outcome is missed or delayed diagnosis of IAI. A missed diagnosis of IAI is defined as a diagnosis of IAI made after the patient is discharged from the hospital (if admitted) or from the ED (if not admitted to the hospital). A delayed diagnosis of IAI is defined as a diagnosis made after patient transfer from the ED to the hospital (including ward/intensive care unit bed). A delayed diagnosis may only be identified in a patient admitted to the hospital. Complications due to the missed/delayed diagnosis will be collected. We anticipate missed/delayed diagnoses to be rare but will nonetheless carefully assess for these as the FAST examination will require acceptance by clinicians that important injuries will not be missed if it is to be incorporated into practice.

Secondary outcome measures will also be collected and analyzed in both study arms. Although these outcomes are not the focus of the analysis, they will be gathered as they are important for assessing the utility of a pediatric trauma evaluation strategy using the FAST. Secondary outcomes include the following: (1) ED length of stay, (2) time to CT, (3) proportion of participants hospitalized and length of hospital stay, (4) proportion with abdominal CTs obtained in the subgroup of children 0 to 3 years old, (5) laparotomy proportion, and (6) physician suspicion of IAI.

ED length of stay is a continuous variable defined as the time (minutes) from ED arrival to ED disposition (ED discharge, hospital admission orders written, transfer to operating suite, or death). Abdominal CT time is defined as the start of the CT, and laparotomy time is defined as the time of entering the operating suite. Both of these are continuous variables and will be measured and compared as such. Time to CT or laparotomy will be measured from the time of ED arrival.

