### {#18b Plans to promote participant retention and complete follow-up}

Guardians of enrolled participants discharged from the ED will be contacted by text/telephone beginning 1 week after discharge from the ED visit for up to 3 months. Evidence from prior studies indicated missed IAIs manifest within 48h of injury [8, 28]. There is no specific retention plan for this study.

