### {#20c Methods in analysis to handle protocol nonadherence and any statistical methods to handle missing data}

We anticipate having no missing data for the primary outcomes of abdominal CT and missed/delayed diagnoses of IAIs.

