### {#23 Frequency and plans for auditing trial conduct}

Remote monitoring visits will be performed at each study site per the study monitoring plan. The purpose of the site monitoring plan is to facilitate site compliance with good clinical practices and Food and Drug Administration guidelines and regulations to verify that the rights and well-being of participants are protected, review any reported adverse events (AE) or serious adverse events (SAEs), and ensure reported data meet attributable, legible, contemporaneous, original, accurate, and complete (ALCOA-C) standards defined as attributable, legible, contemporaneous, original, accurate, complete, consistent, enduring, and verifiable from source documents (source data verification). The trial is also being conducted in compliance with an approved protocol and other applicable regulatory requirements.

At the monitoring visits, the monitor will assess whether the study is being conducted according to the protocol and manual of operations and will educate and advise the participating sites on ways to improve performance. Increased remote or on-site interim monitoring visits may be conducted as necessary based on site performance. The site investigator, lead research coordinator, or other delegated site research staff member will assist with obtaining electronic medical record (EMR) access for all study monitors to allow for source data verification. Any medical records applicable to the study that are received by the site should be available for monitoring as applicable. Site monitoring items are listed in Table 2.

**Table 2 Tab2:** Site monitoring protocol (reviewed at each interim visit as appropriate)

• Verify receipt of all documents and confirm the latest version of the approved protocol and informed consent is being used.
• Discuss protocol updates and revisions as applicable.
• Discuss enrollment issues and targets.
• Confirm via documentation that informed consent for follow-up contact was obtained for each enrolled participant.
• Verify the most recent version of the case report form (CRF) is being completed and review error correction procedures.
• Confirm the proper participants were enrolled (with particular attention to inclusion/exclusion criteria, randomization procedure, potential adverse events, primary efficacy variables, and good clinical practice compliance) and assess if significant protocol deviations have been made or identified by the site.

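### For admitted children, a missed injury means one diagnosed after hospital discharge, but the protocol states no follow-up of these children after discharge

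*Protocol article*

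**What the plan says.** The Outcomes section (item 12) states: "The primary outcomes are the abdominal CT proportion and the proportion of missed/delayed diagnosis of IAIs". It then splits the second outcome in two. For admitted children, "A missed diagnosis of IAI is defined as a diagnosis of IAI made after the patient is discharged from the hospital (if admitted"); for the others the starting point is discharge from the ED. A delayed diagnosis is one made after transfer from the ED into the hospital, and only an admitted child can have one.

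Follow-up is described in three places:
- Participant timeline (item 13): "Hospitalized participants are followed through their hospitalization (up to 30 days from the initial ED visit) to identify outcomes". Guardians of ED-discharged children are approached from day 7, with at most four tries over 3 months.
- Abstract, Methods: "Hospitalized participants will be followed through their stay, and guardians of those discharged from the ED will be contacted after 1 week".
- Retention and follow-up (item 18b): "Guardians of enrolled participants discharged from the ED will be contacted by text/telephone beginning 1 week after discharge from the ED visit". The same paragraph says that earlier studies found missed injuries to show themselves within 48 hours of injury, and adds: "There is no specific retention plan for this study".

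On completeness, item 20c says: "We anticipate having no missing data for the primary outcomes of abdominal CT and missed/delayed diagnoses of IAIs". Table 2 under item 23 has the monitor do the following: "Confirm via documentation that informed consent for follow-up contact was obtained for each enrolled participant".

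**The concern.** The outcome definition and the follow-up schedule do not fit together. In an admitted child the observation described stops at discharge, which is where a missed diagnosis starts to count. Contact after discharge is mentioned three times, each time for ED-discharged children only.

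This outcome is meant to support the claim that FAST reduces CT use safely. The Discussion says it was made primary because clinicians need reassurance about missed injuries. An event that is not looked for lowers the count, which makes either strategy look safer than it is. Whether a child has post-discharge follow-up depends on admission. Admission is decided after randomization and is itself a secondary outcome, so the arms need not be observed equally well.

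**Working it through.** The protocol gives no figure for this outcome that could be reproduced; item 14 says it is too rare to plan on. The total of 4346 rests on the CT outcome alone and is used here only as a count of children.

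**Step 1. Definition against follow-up.**

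| Group | Component | Counts when diagnosed | Stated ascertainment |
|---|---|---|---|
| Sent home from ED | Missed | After ED discharge | Guardian contact from day 7 |
| Admitted | Delayed | After transfer from ED, during the stay | In-hospital follow-up, to day 30 |
| Admitted | Missed | After hospital discharge | None stated |

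Only the third row lacks a stated source.

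**Step 2. What the 48-hour remark does.** If it holds, an admitted child who stays past 48 hours from injury is watched through the relevant window, and a diagnosis made then is counted as delayed. Table 1 admits injuries up to 24 hours old at presentation, so the window closes between 48 − 24 = 24 and 48 hours after arrival. The children exposed to the gap are mainly those whose stay ends before that point. Such stays exist within the trial's definition, because item 12 counts observation status as hospitalization. A child who leaves observation early is in much the same position as a child sent home from the ED, yet only the latter is contacted. In addition, an injury that shows itself within 48 hours need not be diagnosed within the stay.

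**Step 3. Expected events.** Expected total = N × prior rate, with the rates from item 14.
- Single-center trial: 4346 × 1/925 = 4.70 events. The protocol regards that single event as probably a false-positive scan, so this is a generous upper figure.
- Observational study: 4346 × 4/12,044 = 1.44 events.
- At the initial sample size of 3194: 3.45 and 1.06 events.

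These totals cover missed and delayed diagnoses in all children, both arms together. The missed diagnoses in admitted children are an unknown fraction of them.

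**Step 4. What one event does to the interval.** This uses Agresti-Caffo, the protocol's backup method, with 4346/2 = 2173 per arm. Each arm's proportion is p = (x + 1)/(n + 2), and the interval is the difference ± 1.96 × √[p₁(1 − p₁)/(n₁ + 2) + p₂(1 − p₂)/(n₂ + 2)].
- 2 v 2 events: −0.22 to 0.22 percentage points.
- 3 v 2 events: −0.19 to 0.28.
- 4 v 2 events: −0.16 to 0.35.

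One extra event in one arm moves the upper limit from 0.22 to 0.28 points.

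**Step 5. Children without stated post-discharge follow-up.** The share hospitalized is not given. Assuming 20%, 40% or 60%, the numbers are 4346 × 0.20 = 869, 4346 × 0.40 = 1738 and 4346 × 0.60 = 2608. By step 2 these are ceilings, because they include children whose stay covered the 48-hour window.

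**The case against.** The strongest reply is the 48-hour remark: if missed injuries surface that early, most admitted children are still in hospital at the time. This stands as a limit on size. It does not remove the mismatch for short stays.

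Item 22 promises a systematic assessment, in all participants, of complications from missed or delayed diagnosis, and item 19 has coordinators take data from the medical record. A return to the same site might therefore be noticed, and it would go too far to say that such injuries can be found only by luck. But a complication of a missed diagnosis can be assessed only once the diagnosis is known, and no section plans a record search after discharge.

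The 30-day parenthesis could mean follow-up to day 30 whatever the discharge date. The abstract and item 18b do not support that reading. If it is meant, the text should say so. A manual of operations, not shown, may contain more. Even so, the article does not leave follow-up out; it describes it three times, and the description does not match the definition.

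A reader might infer more than the documents support:
- *That unreached ED-discharged children will be counted as event-free.* No section says this. Item 20c states an expectation, not an imputation rule, and detailed handling of missing data commonly belongs in the analysis plan.
- *That 21% to 69% of events will be lost (1/4.70 and 1/1.44).* Those ratios show the weight of one whole event against the expected total. They are not an expected loss, since the gap affects only an unknown part of that total.
- *That the arms will be observed differently.* This needs FAST to change admission, and no figure in the protocol shows that it does.

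**Conclusion.** The point holds in a limited form. The missed component of a primary outcome has no stated ascertainment in admitted children, and the expectation of complete data is not justified for that component. Any error is towards too few events. The loss is unknown in size and probably small, and it falls mainly on short stays if the 48-hour remark is right. It matters because the expected total is only about 1.4 to 4.7 events at the protocol's prior rates. Differential ascertainment is a possibility that depends on FAST altering admission.

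Delayed diagnoses, the CT outcome and the sample size are untouched. Rarity already makes the comparison imprecise, so the gap is not a threat to the trial as a whole. It should be fixed, and soon: enrollment is expected to run to May 2027, and families not contacted now are hard to recover later.

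**What to change.** 1. In item 13, the abstract and item 18b, extend the contact that starts on day 7, with the same number of tries and the same 3-month window, to guardians of hospitalized participants. An equivalent site record check is an alternative.
2. For admitted children who can no longer be contacted, report only the delayed component as ascertained.
3. Amend item 20c so that it no longer anticipates complete data for missed diagnosis, and report the number ascertained in each arm.

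The cost is a short amendment and a modest increase in work for the coordinators. Monitoring already checks follow-up consent for every enrolled participant, so no new consent step appears to be needed. The trial would also have to publish a number not ascertained.

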### {#22 Adverse event reporting and harms}

All research staff were trained on adverse events and adverse event reporting. This included the possibility of a missed or delayed diagnosis of a child with an IAI. We will systematically assess for complications related to missed/delayed diagnosis of IAIs for all participants. All identified harms will be reported in publications, either in the main manuscript or in online supplements.

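### Missed IAI in admitted children has no planned ascertainment: it is defined by a diagnosis after hospital discharge, but their stated follow-up covers only the stay

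*Protocol article*

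**What the plan says.** **Outcome definition.** Section 12 (Outcomes) makes missed or delayed diagnosis of IAI a primary outcome beside abdominal CT use. For an admitted child, the missed component is set by hospital discharge: "A missed diagnosis of IAI is defined as a diagnosis of IAI made after the patient is discharged from the hospital (if admitted"). For a child who is not admitted, it is set by ED discharge. The delayed component concerns admitted children alone: "A delayed diagnosis may only be identified in a patient admitted to the hospital".

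**Follow-up of admitted children.** Section 13 (Participant timeline) states: "Hospitalized participants are followed through their hospitalization (up to 30 days from the initial ED visit) to identify outcomes". The Abstract (Methods) gives the same division between the two groups: "Hospitalized participants will be followed through their stay, and guardians of those discharged from the ED will be contacted after 1 week".

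**Follow-up of children sent home from the ED.** Section 13 states: "The guardians of participants discharged from the ED will be contacted (by telephone or text) at least 7 days from the initial ED visit". It allows four attempts over 3 months from the index visit, starting on day 7. Section 18b describes contact for the same group only: "Guardians of enrolled participants discharged from the ED will be contacted by text/telephone beginning 1 week after discharge from the ED visit".

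**Statements about everyone.** Section 22 (Adverse event reporting and harms) says: "We will systematically assess for complications related to missed/delayed diagnosis of IAIs for all participants". Table 2 in section 23 has the monitor check consent for all: "Confirm via documentation that informed consent for follow-up contact was obtained for each enrolled participant". Section 20c expects no missing data for either primary outcome.

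**The concern.** For an admitted child, the missed component begins at hospital discharge, which is where the stated follow-up ends. If sites follow the schedule as written, nobody is assigned to find out whether an IAI came to light after the child went home. Section 20c nevertheless treats the outcome as complete, and section 22 promises a look at complications in all participants without saying how this is done after an admitted child leaves.

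The Discussion explains that this outcome was made primary so that clinicians can be assured FAST does not increase missed injuries. That assurance is weaker if part of the randomized population is not asked. Whether a child is asked also depends on admission, which is decided after randomization and is itself a secondary outcome.

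**Working it through.** No stated figure is in dispute. The check sets the definition beside the follow-up schedule and then gauges the scale.

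**1. Coverage of each component**

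| Group | Component | Planned way to find it |
|---|---|---|
| Sent home from ED | Missed (after ED discharge) | Guardian contact from day 7 (sections 13, 18b, Abstract) |
| Admitted | Delayed (after leaving the ED for the hospital) | Follow-up through the stay (section 13, Abstract) |
| Admitted | Missed (after hospital discharge) | None stated |

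Three other provisions might fill the last row. Consent for follow-up (section 26a, Table 2) permits contact but schedules none. Section 19 has coordinators enter data from the electronic record, but sets no search after discharge. Section 22 names no method.

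**2. Which admitted children are exposed**

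Section 18b says missed IAIs manifest within 48 h of injury. Table 1 excludes injuries more than 24 h old at presentation, so time from injury to arrival is 0 to 24 h. The time from ED arrival needed to cover 48 h from injury is therefore:

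- arrival at once: 48 − 0 = 48 h
- arrival at 24 h: 48 − 24 = 24 h

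Longer stays cover the window. Shorter ones may not, and section 12 counts observation status as hospitalization with no minimum stay.

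**3. Expected events in the whole trial**

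Inputs from section 14: N = 4346; earlier rates of 1 in 925 (single-center trial) and 4 in 12,044 (observational study). Both rates pool missed with delayed.

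- 4346 × 1/925 = 4.70, or 2.35 per arm
- 4346 × 4/12,044 = 1.44, or 0.72 per arm

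If one event went unseen, it would equal 1/4.70 = 21% to 1/1.44 = 69% of the expected total. This shows how much one event would count, not how likely it is to be lost.

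**4. Children without planned contact after discharge**

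The admitted share is not stated. Assume 20% to 50%:

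- 4346 × 0.20 = 869
- 4346 × 0.50 = 2,173

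If the pooled rates also held among admitted children (a further assumption), they would have between 1.44 × 0.20 = 0.29 and 4.70 × 0.50 = 2.35 missed or delayed events. Delayed diagnoses are seen during the stay, so only part of these could be lost.

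**5. Possible between-arm bias**

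Assume FAST shifts admission by 4 percentage points. With 4346/2 = 2,173 per arm:

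- children whose ascertainment differs: 2,173 × 0.04 = 87
- events among them at the full pooled rates: 87 × 1/925 = 0.09; 87 × 4/12,044 = 0.03

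**The case against.** The strongest reply is that the gap may lie only in the reporting. The article condenses a fuller protocol, and section 23 mentions a manual of operations that is not shown. Consent for follow-up is checked for every participant, records are open to coordinators, and the 30-day phrase in section 13 might be loose wording for follow-up to day 30 whether or not the child has left. Against this, the article is not silent: it states a follow-up route for each group, and the route for admitted children does not reach the outcome as defined. The 30-day phrase reads most naturally as a cap on in-hospital follow-up, and the Abstract's wording supports that reading. If something else was meant, the text should say so.

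The second reply is that little is lost. This largely stands. The 48 h statement protects longer stays, and the outcome is too rare to drive the sample size, as section 14 and the Discussion say. The comparison will be imprecise even with complete follow-up. The single event behind the 1 in 925 rate was also thought likely to be a false-positive CT. But rarity cuts both ways: when so few events are expected, completeness is most of what the outcome can offer.

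Stronger readings are tempting, but the documents do not support them:

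- A reader might infer that a missed IAI in an admitted child can never be observed. A return to a study site could bring one to light; what is absent is a plan to look.
- A reader might infer that these children are scored as event-free by construction. No section says how unascertained children are coded.
- A reader might take section 18b as ending follow-up of admitted children. It does not mention them; only section 13 and the Abstract do.
- A reader might see a flat contradiction with section 22. That section concerns complications and names no method, so it is in tension with the schedule rather than opposed to it.

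**Conclusion.** The point holds as a mismatch between the definition in section 12 and the follow-up in section 13 and the Abstract. The missed component of a primary outcome has no planned ascertainment in admitted children. The no-missing-data expectation in section 20c is not supported for that component.

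The size is modest. The exposure is mainly in short stays, and the number of lost events is probably small. A reader might infer material bias between the arms because admission could differ. On an assumed 4-point shift this comes to about 0.03 to 0.09 events, which is negligible, and listing hospitalization as a secondary outcome does not mean a shift is expected. The case for acting is that only about 1.4 to 4.7 missed or delayed diagnoses are expected in 4346 children, so one unseen event would change what the trial reports on safety. The CT outcome, its test and the sample size are unaffected. Severity: should-fix.

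This rests on the article's text being the operating schedule, on the quoted earlier rates carrying over, and on the assumed 20% to 50% admitted share, which is used for scale only.

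**What to change.** - **Extend the contact.** Amend sections 13 and 18b so that the existing text or telephone contact (from day 7, four attempts at most, within 3 months of the index visit) is also made for guardians of hospitalized participants once they have left the hospital, identically in both arms. Bring the Abstract into line and make clear what the 30-day limit applies to.
- **Admitted children already enrolled.** Use the same contact where the child is still within 3 months of the index visit. Otherwise search the site record, and report this as a limitation because it misses diagnoses made elsewhere.
- **If contact is not extended.** State in sections 12 and 20c that IAI diagnosed after hospital discharge is not systematically ascertained in admitted children, and report missed IAI among ED-discharged children separately.

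The cost is a short amendment and extra texts or calls by coordinators who already make them. Follow-up consent appears to be sought for every participant, but the sponsor should confirm that it covers admitted children. Enrollment is expected to run through May 2027, so an amendment can still benefit children yet to be enrolled.
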